**Fig. 1 Fig1:**
[figure not shown]
Study design

### Participants, setting and procedure

The intervention will be tested on parents with children below five years of age due to the high proportion of drowning of children aged under five years (43 % of deaths among children aged below five years in Bangladesh) [14]. Parents with children aged below five years will be collected from selected rural areas in the Rajshahi district, Bangladesh. College teachers from approximately 15 village schools will be invited to participate with other individuals from their village in a study to test the efficacy of the mobile coach based childhood drowning programme. The participating teachers will schedule one village per hour for screening the eligibility criteria, study information and baseline assessment. The study participants will be recruited by study assistants (graduate students).

The study assistants will invite all the participants from a village to participate in the survey. Furthermore, they will inform other individuals who will be invited to participate in a study to test the efficacy of mobile coach intervention for the prevention of drowning. To decrease the reporting bias, the study assistants will not provide additional information about the purpose of the study before the screening of the eligibility criteria is completed. Afterwards, the participants will be invited to complete the screening. The screening includes the assessment of demographic, environmental, behavioural data, knowledge and awareness about childhood drowning, and ownership of a mobile phone. The inclusion criteria for the study participation are (1) parents who have less than five children, children living with parents, children aged 0–4 and must have a mobile phone in the house. The exclusion criteria are (1) parents who are not available at the time of data collection (after checking the house three times) and children with a physical disability (inability to walk). Subsequently, eligible persons will be informed about the aim of the study, the intervention aims, assessments and data protection. The study information will be provided in paper form by the study assistants. After receiving informed consent, all participants will be given a username and their mobile phone number will be collected.

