## Method/design

### Design and main hypothesis

A two-arm cluster randomised community trial will be conducted to test the efficacy of the mobile coach based intervention for the prevention of childhood drowning among parents with children aged below five years compared to an assessment only control group. In respect of the childhood drowning knowledge, awareness and practice, SMSs, videos, audio messages and images will be sent to participants based on the Ministry of Health and Family Welfare, Bangladesh Government and Centre for Injury Prevention and Research, Bangladesh. The mobile coach will be sent to the participants over a period of six months and data will be gathered at baseline, with a weekly SMS and images, and monthly videos and audio assessment. The main hypothesis is that the integrated intervention will be a more effective and inexpensive way to prevent childhood drowning among children aged below five years, and also increases the parent’s awareness of their children in respect of drowning. At the six-month follow-up, the primary outcome will be the per monthly increase in knowledge, safety awareness and behavioural practice in respect of childhood drowning prevention of the intervention group compared to those in the assessment only control group. The secondary outcome measures will be reducing the incidence of childhood drowning to compare the baseline and end line assessment with the self-efficacy for childhood drowning prevention, and also to determine the risk factors for childhood drowning. An overview of the study design is presented in Fig. 1.

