### Data collection method

#### Baseline survey

Fifteen study assistants and two supervisors will collect data from the two selected union parishad (15 villages) intervention groups and two union parishad (15 villages) control groups. The study assistants will home visit and collect data from the parents through face-to-face interviews using a set of pre-tested questionnaires. The baseline survey will be conducted one month before implementation of the respective intervention packages.

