#### End line survey

The end line survey for the intervention areas will be conducted in the last surveillance round. About 1680 households will be covered by 15 study assistants. Two supervisors will supervise the activities of the study assistants. The end line survey will use the same instruments as those used in the baseline survey and the same procedure will be followed to collect data. The survey will be conducted over 15 days.

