### Data analyses

The data will be entered into SPSS statistical package version 22.0.

The proportion, mean and standard deviation will be used to quantify the level of knowledge, awareness and practice before and after intervention.

The paired *t*-test will be used to examine the effectiveness of the intervention programme by comparing the pre-test and post-test score in respect of knowledge, awareness and practice.

The chi-square test will be worked out to determine the association of the socio-demographic, environmental and behavioural factors with childhood drowning.

In addition, the risk factors for childhood drowning with socio-demographic, environmental and behavioural factors will be determined using multivariate logistic analysis.

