### Outcomes

The outcomes of the study will be to determine the knowledge, awareness and behaviour practices about childhood drowning, as well as the risk factors, and reduce the incidence of childhood drowning. To determine the knowledge pertaining to childhood drowning, five questions about the knowledge of childhood drowning are provided. The questions will be answered YES or NO. A correct answer will score one mark and a zero mark will be given for an incorrect answer. The participants will be classified as having knowledge of drowning if they correctly answer all five questions. Based on those five questions, the total summated score will be calculated. Five questions will be used to measure the awareness about childhood drowning. Based on the five questions, the total summated score will be calculated. The behaviour practices will be divided into supervision practices and swimming ability. In addition, five questions will be used to measure the behaviour practices. Based on the five questions, the total score will be calculated. The study assistants will conduct the six-month follow up assessment by field interviews. The primary outcome will be the monthly assessment of increased knowledge, and safety awareness and practice about childhood drowning. The secondary outcome will be the assessment of reducing the incidence of children drowning to compare the baseline data and end line data, and also to determine the risk factors for childhood drowning. Finally, the outcome variables will be the effects of the mobile coach Intervention on the community in Bangladesh.

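### Enrolment requires a living child aged 0–4, so an unknown share of past fatal drownings is missing from the baseline that the secondary outcome is compared with

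*Protocol article*

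**What the plan says.** **Eligibility.** Under Participants, setting and procedure, the Protocol article admits "parents who have less than five children, children living with parents, children aged 0–4 and must have a mobile phone in the house". The part that matters here is "children living with parents, children aged 0–4". It excludes, among others, "children with a physical disability (inability to walk").

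**Secondary outcome.** The Outcomes section states: "The secondary outcome will be the assessment of reducing the incidence of children drowning to compare the baseline data and end line data". Design and main hypothesis uses the same contrast: "reducing the incidence of childhood drowning to compare the baseline and end line assessment".

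**Data sources.** Baseline data come from interviews with parents: "The baseline survey will be conducted one month before implementation of the respective intervention packages". For the later survey, "The end line survey will use the same instruments as those used in the baseline survey". Between the two, the Injury surveillance section plans monthly household visits, with a form completed for each birth or death.

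**Risk factors.** Under Data analyses, "the risk factors for childhood drowning with socio-demographic, environmental and behavioural factors will be determined using multivariate logistic analysis". The Specific objectives include parental supervision among the behavioural factors and study these factors at pre-test and post-test. Neither section separates drownings before enrolment from drownings after it.

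**The concern.** Any baseline incidence taken from enrolled parents is retrospective and depends on the household still having an under-five at screening. A household that lost its only under-five to drowning is not there to report it. Once enrolled, a household stays in follow-up: no re-screening is described, and deaths are recorded. The two sides of the stated comparison therefore measure different quantities, and the difference pushes towards an apparent rise even if the intervention does nothing.

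Two related effects follow:

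- The Background defines drowning to include morbidity, and the inability-to-walk exclusion can remove severe survivors at baseline. This cannot be quantified from the document.
- If past drownings serve as cases in the logistic analysis, the supervision recorded at the baseline interview comes after the event and may be a reaction to it.

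At stake are the reading of the secondary outcome and the direction of cause in the risk-factor results.

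**Working it through.** **The plan's own figures.** The article gives no baseline drowning incidence, recall window or number of under-fives per household, so there is no figure on this point to reproduce. The sample size reproduces (392; 392 × 1.10 = 431; 431 × 1.95 = 840 per group). It does not bear on the bias and is used below only as the number of households per arm.

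**Step 1. Share of past fatal drownings lost.** Let p_k be the proportion of households with k under-fives before a death. Let r be the per-child risk in households with k ≥ 2 relative to k = 1, and b the chance that another under-five joins the household before screening. A fatal case is lost when k = 1 and no such child joins:

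s = (1 − b) × p_1 / (p_1 + r × Σ_{k≥2} k·p_k)

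All three inputs are assumptions. The value r = 2 borrows the Background's doubled risk in large families and applies it to households with several under-fives.

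| p_1/p_2/p_3 (%) | r = 1, b = 0 | r = 1, b = 15–30 % | r = 2, b = 0 | r = 2, b = 15–30 % |
|---|---|---|---|---|
| 85/14/1 | 73.3 % | 62.3–51.3 % | 57.8 % | 49.1–40.5 % |
| 80/18/2 | 65.6 % | 55.7–45.9 % | 48.8 % | 41.5–34.1 % |
| 70/25/5 | 51.9 % | 44.1–36.3 % | 35.0 % | 29.7–24.5 % |
| 60/32/8 | 40.5 % | 34.5–28.4 % | 25.4 % | 21.6–17.8 % |
| 50/38/12 | 30.9 % | 26.2–21.6 % | 18.2 % | 15.5–12.8 % |

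Example, 70/25/5 with r = 1: 0.70 / (0.70 + 0.50 + 0.15) = 0.70 / 1.35 = 51.9 %. The range is about 13–73 %. Siblings who turn five before screening are not modelled; they would raise the loss.

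**Step 2. Apparent fatal rate ratio, end line over baseline.** With no effect it is 1 / (1 − s):

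- s = 0.128: 1 / 0.872 = 1.15
- s = 0.733: 1 / 0.267 = 3.7

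With a true halving these become about 0.57 and 1.87.

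**Step 3. All drownings.** If a share f of events is fatal and no non-fatal event is lost, the ratio with no effect is 1 / (1 − f·s). Assume f = 0.2–0.5:

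- Lowest: 1 / (1 − 0.2 × 0.128) = 1.03
- Highest: 1 / (1 − 0.5 × 0.733) = 1.58

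**Step 4. How many events this acts on.** The Background gives 156.4 per 100,000 for rural children aged 1–4, treated here as yearly and applied to all under-fives. With an assumed 1 to 1.6 under-fives per household:

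- 840 × 1 × 0.001564 × 0.5 = 0.66 per arm in six months
- 840 × 1.6 × 0.001564 × 0.5 = 1.05 per arm in six months

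**Step 5. Family size.** Take equal per-child risk of 0.00156 and no later births.

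- If the dead child is counted, one-child households show 0 past fatal cases (true risk 1.56 per 1000), and two-child households show 2 × 1.56 = 3.12 per 1000. That is a distorted association.
- If only living under-fives are counted, households with one against two show 0.70 against 0.52, 1.11 against 0.94 and 1.66 against 1.17 per 1000 (structures 80/18/2, 70/25/5 and 60/32/8). The association does not rise with size.

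**Step 6. Surveillance coverage.** Six blocks of 100–150 households make 600–900, against 1680 enrolled. If the six blocks are meant per arm, the total is 1200–1800. The text does not say which.

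**The case against.** The strongest reply is that the effect is too small to matter. With about one fatal drowning per arm in six months, no before/after comparison of deaths could be interpreted, whatever its bias. It can be added that the rule applies equally to both arms, that non-fatal drownings mostly survive the filter, that end line uses the same instruments and procedure as baseline, and that a journal article may leave the recall window to the full protocol.

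Much of this stands. The rarity is real and should be stated, but it limits precision and does not make the two sides comparable. Equal application protects a between-arm comparison; the article words the outcome as before/after. Using the same instruments does not help, because the selection takes place at enrolment, before any instrument is applied. The missing recall window is not held against the article: it affects the size of the loss, not its direction. That follow-up captures deaths in every enrolled household is partly an inference, since the surveillance frame may not cover all 1680.

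A reader might go further and infer any of three things that the document does not support:

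- **That most past fatal drownings are lost.** This holds only if about 70 % or more of households have a single under-five, per-child risk is equal and later births are few. None of this is given.
- **That family size must emerge as a false risk factor.** Step 5 shows this needs past deaths in the model and the dead child counted in family size. Families with one living under-five can report a past fatal case. Family size is also not among the socio-demographic factors in the Specific objectives.
- **That the randomised comparison is biased.** It is not, if it uses events after enrolment.

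**Conclusion.** The point holds in a limited form. The stated baseline-to-end-line comparison is not like with like, because fatal drownings that left no under-five at home are absent from the baseline and countable afterwards. No section corrects for this. The bias runs towards an apparent rise in both arms.

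Its size cannot be fixed from the document. The ranges in Steps 1 to 3 rest on assumed household structures, relative risks, later births and fatal shares. They act on about one expected fatal event per arm.

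The risk-factor analysis is exposed wherever past drownings are used as cases, because exposure is then recorded after the outcome. A family-size artefact is possible but conditional. The change is worth making because it is cheap and removes a known bias from a stated outcome.

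**What to change.** 1. Define the secondary outcome as drownings per child-month after enrolment, recorded by the planned monthly surveillance in the same way in both arms and compared between arms. State whether non-fatal drownings count.
2. Confirm that the surveillance frame covers all 1680 enrolled households, and reconcile the six blocks of 100–150 households with that number.
3. In the risk-factor models, use only post-enrolment events, with factors taken from the baseline interview and a term for arm.
4. State that very few fatal events are expected, about one per arm in six months at the cited rate, so that neither the outcome nor the models are over-read.
5. If a baseline rate is wanted, report it as descriptive only and take it from all listed village households before eligibility is applied.

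Items 1, 3 and 4 are wording changes to the protocol and analysis plan, since monthly visits are already planned. Item 2 costs nothing if coverage is already complete; otherwise it means extending the visits to the remaining enrolled households. Item 5 is optional and needs one question at village listing.

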### Ethical issues

The study protocol has been approved by the University Putra Malaysia medical research ethics committee (No. Reference: UPM/TNCPI/RMC/JKEUPM/1.4.18.1/F1 Date: 11/02/2015). Written informed consent will be obtained from all respondents before collecting data.

### Randomisation and allocation concealment

To avoid spillover effects within the villages, we will conduct a cluster randomised controlled trial using the village as the randomisation unit. Due to the heterogeneity of participants in various disciplines (e.g. gender or educational level), we will use separate randomisation lists for each village (stratified randomisation). Furthermore, for approximate equality of sample size in the study groups, we will use computer generated block randomisation. The study assistants supervising the baseline assessment in the villages will be blinded concerning the group allocation of the village. In addition, group allocation will not be released to the study participants until they provide informed consent, their username, mobile phone number and baseline data. Furthermore, the study assistants conducting the face-to-face interviews at follow up will be blinded when assessing the primary and secondary outcome measures.

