### Study settings and population

Rural Bangladesh is almost demographically and geographically homogeneous. Therefore, the selected sub-districts will be representative of two union parishads (5 villages) for the intervention group and two union parishads (5 villages) for the control group of the rural community of Bangladesh. Parents with children aged 1–4 years in these two groups will comprise the study population.

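### The village cannot be both the unit of randomisation and a stratum with its own list, and describing each arm as two union parishads leaves the allocated unit unclear

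*Protocol article*

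**What the plan says.** The section Randomisation and allocation concealment gives the aim, "To avoid spillover effects within the villages", and the design that follows from it: "we will conduct a cluster randomised controlled trial using the village as the randomisation unit". The abstract also names the village as the unit.

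The next sentence of that section cites differences between participants in gender and education and says "we will use separate randomisation lists for each village (stratified randomisation". It continues: "for approximate equality of sample size in the study groups, we will use computer generated block randomisation". The remark on blinding at baseline then treats group allocation as a property of the village.

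Study settings and population lays out the arms as "two union parishads (5 villages) for the intervention group and two union parishads (5 villages) for the control group". Baseline survey gives "two selected union parishad (15 villages) intervention groups and two union parishad (15 villages) control groups". The union parishads per arm agree; the villages per arm do not.

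Sample size calculation allows for clustering of participants within villages and for no higher level.

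**The concern.** There are two problems, and they differ in certainty.

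The first is a contradiction within the randomisation section. Its reason for stratifying, variation between participants in gender and education, suits allocation of individuals within a village. Carried out that way, neighbours would fall into different arms, controls could see the messages, and the estimated effect would be pulled towards zero.

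The second is the layout. If every study village in a union parishad belongs to one arm, differences between union parishads in water access, services or schooling cannot be separated from the intervention. Analysing by village would then give intervals that are too narrow. The sample size would also have been inflated for the wrong level of clustering.

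**Working it through.** **1. The plan's own sample size.** Inputs from Sample size calculation: proportions 0.55 and 0.45, two-sided 5%, power 80%, 10% non-response, ICC 0.05, and 20 per village in the formula.
- The formula gives 391.3, rounded up to 392 per arm.
- 392 × 1.10 = 431.2, taken as 431.
- Design effect 1 + (20 − 1) × 0.05 = 1.95.
- 431 × 1.95 = 840.45, so 840 reproduces.

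This inflation is for villages of 20 and contains nothing for union parishads. The text beside the formula assumes 30 per village. Dividing 840 by the stated village counts gives 840/5 = 168 or 840/15 = 56, which is neither 20 nor 30.

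**2. The per-village lists.** If the village is randomised whole, each list holds one entry, so blocking and balancing within it mean nothing. If parents are on the list, the village is no longer the unit. No reading satisfies both sentences. As an illustration of the second case, if a share c of controls take up the messages fully, a 10-point difference becomes 10 × (1 − c): 9 points at c = 10% and 7 points at c = 30%. The article gives no value for c, so this range is an assumption.

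**3. Does the layout fit free randomisation of villages?** The chance that every union parishad falls wholly in one arm, under 1:1 randomisation of villages with no strata, is:
- 5 versus 5 villages, assumed split 2/3/2/3 over four union parishads: 4 suitable arrangements out of C(10,5) = 252, or 1.6%.
- 15 versus 15 villages, assumed split 7/8/7/8: 4 out of C(30,15) = 155,117,520, or 2.6 × 10⁻⁸.

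So a layout of this kind fixed in advance, if taken literally, points to allocation by union parishad.

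**4. Consequence if union parishads are the units.**
- Allocations: C(4,2) = 6. Smallest exact two-sided p = 2/6 = 0.33.
- Cluster-level t-test: 2 × 2 − 2 = 2 degrees of freedom.
- Participants per union parishad: 840/2 = 420. At ICC 0.05 the design effect is 1 + 419 × 0.05 = 21.95, and 840/21.95 is about 38 effective participants per arm.
- Standard error: √(2 × 0.2475 × 21.95/840) = 0.114. Noncentrality: 0.10/0.114 = 0.88.

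The article gives no union-level ICC, so the range below is assumed (noncentral t, 840 per arm, 0.55 versus 0.45):

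| Union-level ICC | Power, 2 versus 2 |
|---|---|
| 0.05 | 8.5% |
| 0.02 | 13% |
| 0.01 | 19% |
| 0.005 | 27% |
| 0.001 | 47% |

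**5. Why the village count must also be settled.** With villages as the true units and village ICC 0.05, the same test at 840 per arm has power of 22% with 5 versus 5 villages, 54% with 15 versus 15, and 83% with the 42 versus 42 that 20 per village implies (840/20 = 42). The smallest exact p-values for the two stated layouts are 2/252 = 0.008 and 2/155,117,520 = 1.3 × 10⁻⁸.

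The 0.55 and 0.45 are the plan's own inputs, used here only to stay on its scale. They are the shares of boys and girls among drownings, which is a separate matter.

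**The case against.** Every explicit statement of the unit names the village. The section on settings describes where the study takes place, not an allocation step, and nowhere does the article say that union parishads are randomised, that entire union parishads enter an arm, or that the two pairs are different ones. A reader might infer that three rival units are laid down, or that 2 versus 2 is established. The text does not support either: one unit is stated, and the other two are deduced from loose wording. This part of the objection stands, and the 2-versus-2 consequence is therefore conditional.

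The per-village lists may be a drafting slip, since the same section aims to avoid spillover within villages and speaks of a village's allocation. That makes actual contamination less likely. It does not rescue the sentence, which cannot be carried out alongside the village as unit.

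A reader might also infer from p = 0.33 that no claim at 5% could ever be made. That goes too far. The bound applies to an exact randomisation test. A t-test on 2 degrees of freedom can fall below 0.05, but with the low power shown, and how low depends on an ICC the article does not give.

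**Conclusion.** The contradiction in the randomisation section is certain and needs correction whatever was intended.

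The sections that describe the arms fit poorly with randomisation of villages and disagree on the number of villages. If they mean that all study villages of a union parishad share an arm, arm is confounded with union parishad, the smallest exact two-sided p is 0.33, and union-level power lies between 8.5% and 47% over assumed ICCs of 0.05 to 0.001. The design effect of 1.95 would not cover this. If villages are in fact randomised within all four union parishads, these figures do not apply, but the descriptions of the arms are then wrong. I hold the second part with moderate confidence, because it rests on the plain reading of two descriptive sentences.

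**What to change.** - In Randomisation and allocation concealment, delete the sentence on separate lists per village and state the village as the only unit of allocation.
- Randomise villages from a computer-generated blocked list stratified by union parishad, so that each union parishad contributes villages to both arms. Include union parishad as a fixed effect in the analysis.
- Reword Study settings and population and Baseline survey to match, with one number of villages per arm. The list cannot be drawn up until that number is fixed. Redo the design effect in Sample size calculation for that unit and number.

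Before allocation, the cost is wording and one new list. There are two small downsides. Neighbouring villages in one union parishad may be in different arms, with some sharing of messages. Strata with an odd number of villages will not balance exactly. With only 10 villages split 2/3/2/3 (assumed), 5 per arm and both arms in every stratum, the list has 2 × 2 × (2 × 3 × 3) = 72 allocations, so the smallest exact p is 2/72 = 0.028. This is usable but thin.

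An alternative is to allocate union parishads openly and enrol more of them, which limits sharing between neighbours but costs more.

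If allocation has already been made by union parishad, a new list is not available. In that case, report the union parishad as the unit, analyse at that level, and restate the power and the strength of the conclusion.
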